
### Participants

#### Sample recruitment

The participation in the study will be offered to stable bipolar patients (YMRS ≤ 8, HDRS ≤ 6 for at least one month prior to study entry) who had experienced at least one hypomanic, manic or depressive relapse during the 12 months prior to the study entry. All the participants will be adult patients attending the outpatient mental health clinic of the Hospital Clinic of Barcelona. All participants in both groups must read and agree with the terms and sign an informed consent prior to their inclusion in the study.

The following selection criteria will be considered for the first and third phase:

#### Inclusion criteria

1. Age from 18 to 65 years old, 2. Patients with a current diagnosis of Bipolar disorder type I or type II according to DSM-5 criteria and confirmed with a semi-structured interview (SCID), 3. Hamilton Depression Scale score under or equal to 8 during the last month, 4. Young Mania Rating Scale score under or equal to 6 during the last month, 5. No history of relapses during the previous 3 months but at least 1 relapse during the last year, and 6. Availability of an unlimited smartphone data plan during the 12 following months to avoid extra costs for the participants when using the application.

#### Exclusion criteria

1. Lack of skills to use the offered smartphone or unwillingness to learn them, 2. FAST score above or equal to 20, 3. Current or recent (within the last four years) participation in psychoeducation groups or in individual psychological treatment for the management of bipolar disorder that includes psychoeducational interventions, 4. Obsessive-compulsive disorder according to DSM-5 criteria, 5. Concomitant severe medical condition, 6. Current pharmacological treatment with long-acting antipsychotics and 7. Pregnancy.

### Randomization, data anonymization and blinding

A 5 digits random identification number (IDN) will be generated for all the participants throughout all the phases of the study. The cross-reference of this identification number and the patient identity will be encrypted and stored in a database file. Those patients using the smartphone application will be identified only by the IDN, which will be also the username to access the application. The patient will be asked by the application to enter the username and a password once per smartphone session if he/she is using a current security method to block the phone (code, pattern, face or finger recognition), otherwise the user will have to enter the username and password every time the SIMPLE app is opened.

During the third phase, an independent researcher using the site randomizer.org [50] will randomize the sample to the intervention group or to the control group. Interviews, assessments and focus groups related to the study will be carried out by independent clinicians. Due to ethical considerations, this blinding process will be interrupted if a risk situation is detected through the application during any phase of the study. In this case, the subject will be identified and their therapists will be informed immediately. Exclusion from the study will be discussed depending on the circumstances.

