**Screenshots of SIMPLe 1.0 running in an Android Smartphone.**

### Study design and phases

The studies to evaluate the smartphone application will be carried out in three different but complementary phases as detailed below.**First phase:** A three months lasting feasibility study will be conducted in order to evaluate the use, reliability and patient satisfaction with symptom monitoring (subjective information). Patients under usual treatment will use a smartphone with the SIMPLe version 1.0 application installed. The intervention will be consecutively offered to 30 stable adults (>18 years) fulfilling the inclusion criteria described below. An informed consent will be handled and explained and must be signed in order to participate. Sociodemographic data and standardized clinical as well as functional assessments will be administered at baseline and monthly for three months. Assessments will include present manic symptoms using the Young Mania Rating Scale (YMRS) [40,41], depressive symptoms using the Hamilton depression Rating Scale (HDRS) [42,43], biological rhythms using the biological rhythms interview of assessment in neuropsychiatry (BRIAN) [44,45] and treatment adherence using the Morisky Green 8-item test [46]. A smartphone device with the SIMPLe 1.0 application pre-installed, will be given to the participants for free during the study with the mandatory condition that it has to be their main mobile-phone during the next 3 months. In the case the patient accepts to participate but doesn’t want to switch from his/her current smartphone, he/she will be offered the possibility to download the SIMPLe 1.0 application from the Application Store and a username and password will be given. The subject will receive a customizable automatic reminder in their smartphone to answer both daily and weekly questionnaires based on DSM-5 criteria for a manic, hypomanic, mixed or depressive episodes. The data obtained will be registered online. During this period of time, the subjects will receive daily customized psychoeducative messages based on the information collected by the application using an algorithm designed by our team. Feasibility and satisfaction will be assessed with the application usage log data and with an electronic survey. Reliability will be analyzed comparing the clinical assessments made by a psychiatrist and the information about mood state collected by the application**Second phase:** Three different focus groups (patients, psychiatrists and psychologists, software engineers and graphical designers) of 3 sessions each will be held to discuss the experience with the SIMPLE 1.0 app and recollect suggestions and bugs. Additionally, individual personal interviews with each SIMPLE 1.0 user will also collect qualitative information about the application and suggestions. Taking into consideration the information collected from participants in the first phase, the application will be adapted and improved with the addition of objective information (signs) monitoring modules using mobile usage parameters and the built-in actimetry sensors.**Third phase:** A six months randomized controlled trial with an intervention and a control arm including 74 patients each. An initial evaluation in both groups will be carried out recollecting sociodemographic data and using standardized clinical as well as functional assessments. This evaluation will be repeated at three, six and twelve months from baseline. The assessments will include present manic symptoms using the Young Mania Rating Scale (YMRS), depressive symptoms using the Hamilton depression Rating Scale (HDRS), functional impairment using the Functioning assessment short test (FAST) [47], biological rhythms using the biological rhythms interview of assessment in neuropsychiatry (BRIAN), quality of life measured by World Health Organization quality of life assessment (WHOQOL-BREF) [48] and treatment adherence using the Morisky Green 8-item test. During the follow-up the number of relapses, inpatient admissions, outpatient consultations, emergency rooms consultations and suicide attempts will be registered.**Intervention arm (SIMPLe 2.0 + TAU):** The experimental group will use the application SIMPLe 2.0 and will keep receiving their usual pharmacological treatment. A smartphone device with the SIMPLe 2.0 application pre-installed, will be given to the participants for free during the study with the mandatory condition that it has to be their main mobile-phone during the next 3 months. In the case the patient accepts to participate but does not want to switch from their current smartphone, they will be offered the possibility to download the SIMPLe 2.0 application from the Application Store and a username and password will be assigned. The self-mood assessments will adopt a similar approach to the SIMPLe 1.0 app. Additionally this information will be complemented with automatically recorded patients activity data which will include smartphone usage, telephone calls made (number of independent calls and total time), social network apps usage, and physical activity measured by the built-in actimeter. Patients will receive daily psychoeducative messages based on the data recollected by the application. Relapse risk will be calculated using an algorithm including both subjective and objective data. The clinical team will be contacted with an e-mail if there is moderate or high risk for an oncoming episode and the patient will be offered the outpatient or emergency for assistance.**Treatment as usual arm (TAU):** The treatment as usual (TAU) group will be followed-up with their standard treatment following the Barcelona Bipolar Disorders Program protocol [49].

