### Power and sample calculation

We adopted a conservative approach for the first phase of the study to ensure more close qualitative feedback. Accordingly we calculated a sample size of 30 based in the recommendations for internal pilot studies from Kieser&Friede [51]. For the third phase, a significance level of 0.05, power of 0.8 and a minimal detectable difference of 0.5 and an expected drop-out of 15% was set, which resulted according to the design in two arms of 74 patients each [52].

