### Statistical analysis

During the first phase, a descriptive analysis of socio-demographic and clinical variables will be conducted, including mean age, sex, marital status, employment status, family psychiatric history, follow up time, number of episodes, predominant polarity, substance abuse and comorbid medical and psychiatric diagnoses. Feasibility will be evaluated analyzing the frequency of daily and weekly tests completed, if important differences in baseline characteristics between adherent and not adherent users are detected, this will be further controlled by regression analyses. The results of the satisfaction survey will be estimated analyzing the percentage of answers and the differences among the different categories using Chi-square analysis. Additionally, a Pearson correlation analysis will be carried out between the results of the assessments during the 3 month period and the results of the application tests to evaluate the clinical reliability between the two methods.

At the third phase, survival analysis with multivariate data analysis will be carried out to assess several covariates simultaneously and explore relationships between socio-demographic, clinical variables and assessments scores with relapses in each group (Kaplan-Meier). Similarly, differences among the different assessments will be analyzed with multivariate survival analysis (Cox regression). Similarly as in the first phase, a Pearson correlation analysis will be carried out between the results of the assessments and completed application tests. All the analyses will be two-tailed with an alpha set at p < 0.05. Additionally, last observation carried-forward intention to treat analyses will be performed.

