### Ethical and safety considerations

One of the main concerns during the development of the application was patient safety. Hence, the application incorporated a function which automatically notify the mental health team about suicide risk and give the patients the possibility to make a call to the emergency services from their own smartphone. Depending on the severity of the symptoms or if suicidal risk is detected, the blinding of the protocol will be broken and the case will be immediately discussed with their therapists.

In order to ensure participants’ confidentiality during the study and the transmission of personal data we adopted a security protocol using the IDN, as it has been previously described, which is in accordance to the local spanish laws (Ley orgánica de Protección de Datos de Carácter Personal (15/1999)). The username and password for the application will be requested every time the application is used if the user didn’t active a smartphone lock system, otherwise it could be used without entering the username and password. Additionally, the study protocol was evaluated and approved (Reg. HCB/2014/0403) by the Hospital Clinic of Barcelona ethical committee to ensure is accordance to the Helsinki Declaration. The study was registered at Clinicaltrials.gov with the identifier NCT02258711 on October 2014.

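### In phase 3, app alerts add surveillance, an unblinding trigger and prompted visits in the intervention arm only, so relapse and service use are not ascertained alike

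*Protocol article*

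**What the plan says.** *Blinding.* The section Randomization, data anonymization and blinding assigns interviews and assessments to independent clinicians. It continues: "Due to ethical considerations, this blinding process will be interrupted if a risk situation is detected through the application during any phase of the study". The subject is then identified and the therapists are told. Ethical and safety considerations returns to the matter with a trigger worded as symptom severity or suicidal risk, in which case "the blinding of the protocol will be broken and the case will be immediately discussed with their therapists". That sentence does not name the app, although it comes directly after the description of the app's notification function.

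*The app arm.* Study design and phases (third phase) gives the app to the intervention arm only. An algorithm calculates relapse risk. "The clinical team will be contacted with an e-mail if there is moderate or high risk for an oncoming episode", and the patient is then offered outpatient or emergency assistance. Self-assessment follows the earlier app version, which Application development describes as daily questions plus a DSM-5-based test, weekly or after a mood change.

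*The control arm.* Control patients are followed under the standard programme.

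*Both arms.* The same evaluation is made at baseline and at 3, 6 and 12 months. "During the follow-up the number of relapses, inpatient admissions, outpatient consultations, emergency rooms consultations and suicide attempts will be registered". The Background hypothesis includes lower use of health resources, and Statistical analysis makes relapse the event in the survival analysis.

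**The concern.** A survival comparison of relapse needs events to be found and dated in the same way in both arms. Here one arm has a daily signal, a risk algorithm and a route into the clinic between scheduled visits, and the other does not. Milder episodes could be found more often, or dated earlier, in the app arm.

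The Discussion acknowledges that patients are not blinded, so the independent assessor is the main remaining safeguard. If the app trigger removes that safeguard, it does so for intervention patients at the highest risk of the outcome.

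Consultations are a hypothesised benefit, yet the intervention itself generates some of them, and the article describes no record of which ones. What is at stake is whether a difference in relapse or service use reflects the app's effect, closer observation, or a rater who knows the arm. A later analysis cannot restore blinding that was lost, or identify prompted visits that were never marked.

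**Working it through.** **1. Which ascertainment routes exist in which arm (phase 3)**

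| Route | App + TAU | TAU | Section |
|---|---|---|---|
| Evaluation at 0, 3, 6, 12 months | yes | yes | Study design and phases |
| Registration of relapses, admissions, visits | yes | yes | Study design and phases |
| Daily and weekly self-tests, risk algorithm | yes | no | Study design and phases; Application development |
| Risk e-mail and offered visit | yes | no | Study design and phases |
| Unblinding on an app-detected risk | yes | not possible | Randomization, data anonymization and blinding |
| Unblinding on severity or suicidal risk | yes | not excluded by the wording | Ethical and safety considerations |

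The first two rows are symmetric. The next three are not. The last conflicts with the one above it on what the trigger is.

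**2. The plan's own figure**

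Power and sample calculation states "a significance level of 0.05, power of 0.8 and a minimal detectable difference of 0.5 and an expected drop-out of 15% was set", giving 74 per arm; the tests are two-sided. Read as a standardised mean difference (the scale is not stated):

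n = 2(1.96 + 0.842)² / 0.5² = 62.79, and 62.79 / 0.85 = 73.9, so 74 per arm.

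The figure is reproduced, and this point does not depend on it. It supplies only the number of completers used below: 74 × 0.85 = 62.9, taken as 63 per arm.

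**3. Illustration of unequal detection**

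The article gives no relapse or detection rates. Everything in this step is assumed: the same true relapse risk p in both arms, app-arm detection of 100%, control detection s of 90%, 80% or 70%, and control relapses that are missed stay missed.

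Observed risks are p·s (control) and p (app), so the observed risk ratio is 1/s. The chance of a significant result against the app is

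Φ[(d − 1.96·SE₀)/SE₁], where d = p − p·s, SE₀ is the pooled and SE₁ the unpooled standard error with 63 per arm.

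Example with p = 0.40 and s = 0.80: risks 0.32 and 0.40, d = 0.08, SE₀ = √(2 × 0.36 × 0.64/63) = 0.0855, SE₁ = √((0.2176 + 0.24)/63) = 0.0852. Φ[(0.08 − 0.1676)/0.0852] = Φ(−1.03) = 0.152.

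| Control detection | Observed risk ratio | p = 0.3 | p = 0.4 | p = 0.5 |
|---|---|---|---|---|
| 90% | 1.11 | 0.056 | 0.067 | 0.081 |
| 80% | 1.25 | 0.114 | 0.152 | 0.202 |
| 70% | 1.43 | 0.210 | 0.294 | 0.397 |

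The nominal rate in that one direction is 0.025.

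With a real benefit (true risk ratio 0.5), power at control detection of 100%, 90%, 80% and 70% is:

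- control risk 0.5: 0.83, 0.66, 0.44, 0.23
- control risk 0.4: 0.69, 0.52, 0.33, 0.18

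A simulated time-to-event version (4000 trials, 74 per arm, 40% control relapse, 15% random drop-out) agrees. With no true effect, the hazard ratio is 1.01, 1.14, 1.32 and 1.55 at control detection of 100%, 90%, 80% and 70%.

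**4. What the illustration leaves out**

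It models neither unblinded rating nor prompted consultations. An assessor who knows the arm could rate in either direction. If the planned visits recover the control relapses missed in between, control detection approaches 100% and the distortion in the count disappears (hazard ratio 1.01). The figures show sensitivity to the assumption and are not a forecast.

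**The case against.** Several objections have force.

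- A reader might infer that relapses are detected in one arm only. The article does not support that: evaluations and relapse registration cover both arms, and control patients attend a specialised programme. Only the additional between-visit detection is one-armed.
- A reader might infer that outcome assessors are certainly unblinded for app patients and never for controls. Only therapists are named as informed, and the trigger in Ethical and safety considerations is not expressly tied to the app. Loss of assessor blinding is still the natural reading, because the interruption clause follows directly on the sentence about independent clinicians and nothing says they stay blind.
- An alert warns of a coming episode and is part of the treatment mechanism. Nowhere is an alert counted as a relapse. The relapse definition may also stand in a full protocol that is not shown.
- Visits that the app generates are a real consequence of the intervention and belong in an intention-to-treat total. Looking only at unprompted visits could flatter the app, since prompted visits may replace others.
- Limiting relapses to those established at scheduled visits would lose documented episodes in patients who leave before the next visit, with 15% drop-out expected. App users who see daily mood graphs may also recall episodes better.

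These narrow the point and shape the remedy. They do not remove it: the app-based trigger and the alert pathway are stated rules, and both apply in one arm.

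**Conclusion.** The point holds as an asymmetry of ascertainment. Following the article as written, between-visit surveillance, an app-based unblinding trigger and prompted visits occur in the intervention arm only, while relapse and service use are compared between arms. Assessor blinding can lapse selectively for app patients at highest risk; that is a strong inference from the wording and is not stated outright.

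Under the assumed detection rates, a null effect would appear as a risk ratio of 1.11 to 1.43 against the app. It would be tempting to conclude that the trial is biased towards harm by that amount. The article does not support this: the rates are assumptions, scheduled visits may recover missed episodes, and unblinded rating is not modelled. Size and net direction remain undetermined, which is itself a reason to settle the rules before phase 3 begins.

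**What to change.** 1. Reconcile the two unblinding statements on what triggers unblinding and who is unblinded. State that an alert identifies the patient to the treating team only, and that the independent outcome assessor stays blind to arm and to app data. Alerts and therapist notification are unchanged.
2. Have blind assessors establish relapse at the planned 3-, 6- and 12-month visits, by the same criteria and the same interview over the preceding interval in both arms. Also use admissions and clinically documented episodes from both arms, so that relapses before drop-out are kept. State that an app signal alone is not a relapse.
3. Record for each consultation whether the app prompted it. Keep total consultations as the intention-to-treat comparison, and report admissions and non-prompted consultations as supplementary.

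The cost is protocol wording, one extra field in the consultation record and a fixed interview at visits already planned. The downside is that dates of mild relapses rest partly on recall, which may not be equally good in the two arms. Clinically documented episodes may themselves come to light more often in the app arm, so some asymmetry remains and should be acknowledged when the results are reported.

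### Exclusion after an app-detected risk can arise only in the app arm, so the phase 3 relapse comparison can be biased in the app's favour unless follow-up and event counting continue

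*Protocol article*

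**What the plan says.** The rule is in the Protocol article under Randomization, data anonymization and blinding. For ethical reasons, "this blinding process will be interrupted if a risk situation is detected through the application during any phase of the study". The patient is then identified and the therapists are informed. The paragraph ends: "Exclusion from the study will be discussed depending on the circumstances". It gives no criteria and does not say whether follow-up continues.

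Ethical and safety considerations restates the unblinding trigger: "Depending on the severity of the symptoms or if suicidal risk is detected, the blinding of the protocol will be broken".

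Study design and phases describes the two phase 3 arms. For the intervention arm: "The experimental group will use the application SIMPLe 2.0 and will keep receiving their usual pharmacological treatment". For control: "The treatment as usual (TAU) group will be followed-up with their standard treatment following the Barcelona Bipolar Disorders Program protocol". In the intervention arm, "Relapse risk will be calculated using an algorithm including both subjective and objective data", and "The clinical team will be contacted with an e-mail if there is moderate or high risk for an oncoming episode".

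The Statistical analysis section plans Kaplan-Meier and Cox analyses of relapse for phase 3, names no analysis population for them, and closes with: "Additionally, last observation carried-forward intention to treat analyses will be performed".

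**The concern.** The trigger for possible exclusion depends on randomised assignment. Control patients have no app, so they cannot have an app-detected risk, and no parallel route is stated for them. The trigger is also related to the outcome: severe symptoms and suicidal risk, and possibly a forecast episode, mark patients more likely than average to relapse.

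Removing such patients from one arm after randomisation breaks the comparison that randomisation set up. Censoring them at exclusion does not help, because that censoring is informative: those censored have a higher relapse hazard than those who stay. At stake is an apparent relapse benefit produced partly by who was kept in the data.

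**Working it through.** **Inputs from the Protocol article.** 74 patients per arm, two-sided alpha 0.05, power 0.8, difference 0.5, drop-out 15% (Power and sample calculation; Statistical analysis). The 74 reproduces if 0.5 is read as a standardised difference: 2 × ((1.960 + 0.842)/0.5)² = 62.8 per arm, and 62.8/0.85 = 73.9. Rounding up to 63 first gives 75. The sample size is not at issue.

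**Assumptions not in the document.** No true effect; relapse proportion p = 0.40 in both arms; a fraction f of app-arm would-be relapsers excluded before their relapse is recorded; no non-relapsers excluded.

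**Patients dropped at exclusion.** Observed app-arm relapse is p(1 − f)/(1 − pf), on n₁ = 74(1 − pf) patients. With d the difference from 0.40 and SE the unpooled standard error against 74 controls, the two-sided rejection probability is Φ(−1.96 − d/SE) + Φ(−1.96 + d/SE).

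- f = 0.125: 74 × 0.4 × 0.125 = 3.7 patients excluded. Observed 0.35/0.95 = 36.8%; n₁ = 70.3; SE = 0.0809; d/SE = −0.390. Rejection 0.0582 + 0.0094 = 0.068.
- f = 0.25: 7.4 patients excluded. Observed 0.30/0.90 = 33.3%; n₁ = 66.6; SE = 0.0811; d/SE = −0.822. Rejection 0.1276 + 0.0027 = 0.130.

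At f = 0.125 about 86% of the false positives favour the app (0.058/0.068); at f = 0.25 nearly all do.

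**Last observation carried forward.** If excluded patients are kept but carried forward as relapse-free, the observed proportion is p(1 − f), which is lower still. At p = 0.40 and f = 0.20 (about 6 patients), dropping gives 0.32/0.92 = 34.8% and carrying forward gives 32.0%, against 40% in control.

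**Check with the planned type of analysis.** A log-rank simulation used 74 per arm, no true effect, exponential relapse times to 12 months, 4,000 runs per scenario, and censoring of excluded patients just before relapse. Across p = 0.2 to 0.5:

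| f | Apparent hazard ratio | Chance of a significant result favouring the app (nominal 2.5%) |
|---|---|---|
| 10% | about 0.90 | 4–6% |
| 20% | about 0.80 | 8–15% |
| 30% | about 0.70 | 14–28% |

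**If non-relapsers are excluded too.** With p = 0.40, 25% of relapsers and 12.5% of non-relapsers excluded, the observed proportion is 0.30/(0.30 + 0.525) = 36.4%, not 33.3%. With n₁ = 61.05, SE = 0.0839 and d/SE = −0.434, rejection is 0.0635 + 0.0083 = 0.072. If both groups are excluded at the same rate, the expected proportions are equal and this bias is zero.

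**If everyone is followed and counted (f = 0).** Under no true effect the expected proportions are equal and the nominal 5% level applies.

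**The case against.** The strongest reply is that the sentence only permits a discussion. No exclusion may ever occur, and the provision exists for patient safety. That is right as far as it goes, so the relapse comparison can be biased; the document does not show that it will be.

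A reader might infer that patients flagged for an oncoming episode are the ones excluded. The article does not say so. That alert leads to an e-mail to the team and an offer of outpatient or emergency assistance, with no mention of unblinding or exclusion. The exclusion sentence refers to an undefined risk situation, and the restated unblinding trigger is symptom severity or suicidal risk. Suicidal risk overlaps with relapse but is not the same. A patient with severe symptoms may already have relapsed, and relapses are to be registered during follow-up, so the event could be counted before any exclusion. The favourable direction requires that it was not.

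A reader might also infer that the main analysis drops these patients because intention-to-treat is introduced as an addition. The article names no population for the Kaplan-Meier and Cox analyses, the adverb may be a plain connective, and the analysis set is commonly left to the SAP. That inference is not supported. Calling the stated intention-to-treat analysis the main one would not be enough either, because it carries the last observation forward.

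On size, the illustration excludes would-be relapsers only, which amounts to assuming no false alarms. Yet the Application development section says the questionnaires had not been validated in a real-world clinical setting. More dramatic figures are easy to produce: f = 0.5 gives 25% against 40% and a rejection rate of 46.6%. But that removes 14.8 of 74 patients, 20% of the arm, against 15% planned drop-out from all causes.

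What stands after this is the stated rule: a discretionary exit from the study, open in one arm only, on a trigger related to the outcome, with no statement that follow-up continues. An analysis plan cannot recover relapses that were never observed.

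**Conclusion.** The point holds as a risk of bias in the app's favour, conditional on exclusions taking place in phase 3 and on relapse not having been recorded beforehand. Neither censoring at exclusion nor the carried-forward intention-to-treat analysis removes it.

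The size cannot be fixed from the document. With 40% relapse, no true effect and only would-be relapsers excluded, losing about 4 to 7 app-arm patients this way moves observed relapse to between 36.8% and 33.3% against 40%, and the two-sided error rate from 5% to about 7% to 13%. Exclusion of non-relapsers reduces this, to nothing if the rates are equal. The document does not support the firmer claims that relapse is biased, that patients about to relapse are selected, or that the main analysis leaves them out.

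**What to change.** State for phase 3 that, whatever is decided clinically or about app use after an alert, the patient remains in the scheduled 3-, 6- and 12-month evaluations unless consent is withdrawn. This takes no position on how alerts are handled, on unblinding, or on whether the patient goes on using the app.

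State that the main Kaplan-Meier and Cox analysis includes all randomised patients in their assigned arm, with observed post-alert relapses counted and excluded patients not carried forward as relapse-free. Report the number of alerts, app discontinuations and any exclusions.

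The cost is a few sentences and continued follow-up of patients who stop the app, at visits already scheduled. It should be settled before phase 3 randomisation, because follow-up that has been stopped cannot be relied on to be recovered.
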